## Abstract

**Background:**

In 2014 the Swedish government assigned to The Public Health Agency of Sweden to conduct studies to evaluate optimal use of existing antibiotic agents. The aim is to optimize drug use and dosing regimens to improve the clinical efficacy. The present study was selected following a structured prioritizing process by independent experts.

**Methods:**

This phase IV study is a randomized, open-label, multicenter study with non-inferiority design regarding the therapeutic use of penicillin V with two parallel groups. The overall aim is to study if the total exposure with penicillin V can be reduced from 1000 mg three times daily for 10 days to 800 mg four times daily for 5 days when treating *Streptococcus pyogenes* (Lancefield group A) pharyngotonsillitis. Patients will be recruited from 17 primary health care centers in Sweden. Adult men and women, youth and children ≥6 years of age who consult for sore throat and is judged to have a pharyngotonsillitis, with 3–4 Centor criteria and a positive rapid test for group A streptococci, will be included in the study. The primary outcome is clinical cure 5–7 days after discontinuation of antibiotic treatment. Follow-up controls will be done by telephone after 1 and 3 months. Throat symptoms, potential relapses and complications will be monitored, as well as adverse events. Patients (*n* = 432) will be included during 2 years.

**Discussion:**

In the era of increasing antimicrobial resistance and the shortage of new antimicrobial agents it is necessary to revisit optimal usage of old antibiotics. Old antimicrobial drugs are often associated with inadequate knowledge on pharmacokinetics and pharmacodynamics and lack of optimized dosing regimens based on randomized controlled clinical trials. If a shorter and more potent treatment regimen is shown to be equivalent with the normal 10 day regimen this can imply great advantages for both patients (adherence, adverse events, resistance) and the community (resistance, drug costs).

**Trial registration:**

EudraCT number 2015-001752-30. Protocol FoHM/Tonsillit2015 date 22 June 2015, version 2. Approved by MPA of Sweden 3 July 2015, Approved by Regional Ethical Review Board in Lund, 25 June 2015.

## Background

In 2014 the Swedish government assigned to The Public Health Agency of Sweden to conduct studies to evaluate existing antibiotic agents from new perspectives. The aim is to optimise drug use and dosage regimens to improve the clinical efficacy of existing antibiotics, and to reduce ecological disturbances in the normal microbiota. The clinical trial described below is one of the projects prioritized by independent experts within this assignment.

Pharyngotonsillitis is one of the most common infections in primary health care (PHC) in Sweden [1] and accounts for about 20 % of all antibiotic prescriptions within PHC [2]. The estimated number of patients in Sweden treated for pharyngotonsillitis is about 400,000 each year [3]. Streptococcus group A (GAS) is the most common bacterial etiology and also the dominating reason for antibiotic treatment [3]. According to the Swedish guidelines the recommendation is to treat pharyngotonsillitis with phenoxymethylpenicillin (penicillin V) if 3–4 Centor criteria [2] and GAS is present [3]. The recommended dose for adults is 1000 mg penicillin V three times daily for 10 days which corresponds to about 12 t of penicillin V each year in Sweden, calculated on the basis of adult doses. The infection is most frequent among school children and young adults, resulting in a somewhat lower total amount of consumption [4].

According to present European and American guidelines, 10 days penicillin treatment is generally recommended as first line treatment of streptococcal pharyngotonsillitis [5, 6]. The historical reason for 10 days treatment duration with penicillin is mainly to avoid serious complications like acute rheumatic fever and glomerulonephritis. These conditions are currently extremely rare in western countries [7]. According to a Cochrane report from 2012 patients recover without antibiotic therapy but treatment is sometimes advised to hasten clinical resolution and prevent suppurative sequelae, like peritonsillitis, acute otitis media or sinusitis. Clinical studies on shorter treatment duration with penicillin for streptococcal pharyngotonsillitis are encouraged [8].

There are few published studies comparing 10 days treatment duration with shorter treatment durations with penicillin V. Three studies which were published in the 1980s have been identified. Five versus 10 days (250 mg three times daily and 800 mg twice daily respectively) [9, 10] and 7 versus 10 days (500 mg three times daily) [11] were studied. All of the studies concluded that 10 days of treatment was preferable but in the light of current knowledge of pharmacokinetics and pharmacodynamics (PK/PD) the doses used in these studies were suboptimal. The effect of beta-lactam antibiotics is dependent on time above the minimum inhibitory concentration (MIC) of the unbound drug concentration in serum (free drug time above MIC; fT > MIC). Usually, the target is that 95–99 % of the population should achieve a fT > MIC of around 30–40 % for non-severe infections [12], also expressed as the population target attainment for a given target. For beta-lactams a more frequent dosing is preferred and the dosing interval is more critical than the size of the dose [12]. The dosing regimen 800 mg four times daily provides better target attainment compared to 1000 mg three times daily (33 % fT > MIC compared to 25 % fT > MIC at the breakpoint MIC 0.25 mg/L). Our hypothesis is that the experimental dosage regimen 800 mg four times daily gives at least the same efficacy, possibly better patient adherence and a significantly lower total exposure.

In the present study we will examine if penicillin V given four times daily for 5 days is non-inferior to the currently recommended dose regimen of 10 days to patients with pharyngotonsillitis caused by streptococcus group A. Reducing the treatment duration to 5 days will almost halve the consumption of penicillin V for this indication. A shorter treatment duration may potentially improve patient adherence [13], cause less effect on the human microbiota [14] as well as lower medicinal costs for patients and community.

## Methods

### Aim

The overall aim is to study if the total exposure with antibiotics can be reduced from 1000 mg three times daily for 10 days to 800 mg four times daily for 5 days when treating streptococcus group A pharyngotonsillitis with penicillin V.

### Design

This Phase IV study is a randomized, open-label, multicenter study with non-inferiority design regarding the therapeutic use of penicillin V with two parallel groups.

### Setting

Patients will be recruited from 17 primary health care centers (PHCC) in the counties of Skåne, Kronoberg and Västra Götaland in the southern of Sweden. The PHCCs are representing both urban and rural regions.

### Characteristics of the patients

#### Inclusion criteria

Adult men and women, youth and children ≥6 years of age who are seeking a PHCC for sore throat with suspected tonsillitis and meeting the criteria in accordance with current treatment recommendations for streptococcal pharyngotonsillitis, i.e. 3–4 Centor criteria (fever ≥ 38.5, tender lymph nodes, coatings of the tonsils and absence of cough) and a positive rapid antigen detection test (RADT) for GAS will be included in the study [15].

#### Exclusion criteria

A patient is not eligible for inclusion if any of the following criteria apply: 1) Signs of serious illness according to pre-specified criteria, 2) hypersensitivity to penicillin, 3) chronic illness that significantly impair the immune system, 4) immunomodulating treatment, 5) treatment with antibiotics for pharyngotonsillitis during the last month (relapse), 6) any antibiotic treatment during the last 72 h before inclusion, 7) difficulty swallowing tablets, 8) any other cause which, according to the physician’s judgment, makes it unsuitable for the patient to participate in the study.

#### Intervention

Patients will be randomized to treatment with penicillin V four times daily for 5 days or three times daily for 10 days. The dosages for different weight groups are presented in Table 1.

**Table 1 Tab1:** Penicillin V dosing schedule

Body weight	Dosage 5 days treatment	Dosage 10 days treatment
>40 kg	800 mg × 4	1000 mg × 3
20–40 kg	500 mg × 4	500 mg × 3
10–20 kg	250 mg × 4	250 mg × 3

#### Randomization

Randomization within blocks for each PHCC separately was performed by a statistician at The Public Health Agency of Sweden. Sealed envelopes with unique numbers and allocated treatment were distributed to each of the 17 participating PHCCs.

### Context and procedure

Study procedures are presented in Table 2.

**Table 2 Tab2:** Study procedures for both intervention groups, penicillin V given four times daily for 5 days or three times daily for 10 days

	Baseline	5–7 days after penicillin V treatment discontinuation.	1 month (by telephone)	3 months (by telephone)
Clinical judgement by physician	X	X		
Anamnesis	X			
Written informed consent	X			
Inclusion/exclusion criteria	X			
Concomitant drug treatment	X	X		
Rapid antigen detection test (RADT)	X	X		
Throat swab culture	X	X		
Evaluation of primary endpoint		X		
Monitoring adverse events		X	X^a^	
Monitoring relapses		X	X	
Monitoring complications			X	X

^a^Follow-up of adverse events which were ongoing at previous contact

#### Visit one

Patients presenting with sore throat will be clinically examined by a physician. In case of suspected faryngotonsillitis and 3–4 Centor criteria a RADT for GAS will be performed. Patients with a positive RADT test for GAS who meet all the inclusion criteria, and none of the exclusion criteria, will be asked to participate in the trial. After signed informed consent, by patient or guardian, the patient will be asked about medical history, demographic data, previous antibiotic exposure and concomitant drug treatment.

A throat swab for semi quantitative cultures of streptococcus group A, C and G will be performed.

After randomization to intervention group 5 or 10 days the physician prescribes penicillin V which the patient will retrieve from the pharmacy. A patient diary is handed out which the patient or guardian is asked to fill in until the follow-up visit, five to seven days after treatment discontinuation.

Demographic data and clinical data will be recorded in a case report form (CRF) by study personnel. In addition, data regarding intake of penicillin V doses and analgesics, presence of sore throat and fever, adverse events etc. is filled in daily by each patient or guardian in the diary.

#### Test-of-cure visit

A test-of cure (TOC) visit will be performed at the PHCC 5 to 7 days after completion of antibiotic treatment. Clinical judgement of throat status, a new RADT and culture, and recording of adverse events will be performed.

#### Follow-up controls

Follow-up controls will be done by a telephone call 1 month (28–35 days) and 3 months after the last treatment day. Throat symptoms, potential relapses and complications will be monitored as well as adverse events ongoing at previous visits.

### Outcomes

#### Primary outcomes

The primary outcome is clinical cure 5–7 days after discontinuation of antibiotic treatment (TOC). The patients will be asked about throat symptoms and a clinical judgement will be performed by the investigator. Clinical cure is defined as complete recovery without remaining/residual symptoms or clinical findings of pharyngotonsillitis or symptomatic relapse at TOC [15].

#### Secondary outcomes

The secondary outcomes are bacteriological eradication according to the culture taken at the TOC, time to relief of symptoms according to the patient diary, frequency of relapses one month after first diagnosis, frequency of complications during the study period as well as pattern of adverse events.

### Definitions

Definitions of outcome measures are presented in Table 3.

**Table 3 Tab3:** Definitions of outcome measures

Term	Definition
Clinical cure	Clinical judgement by physician 5–7 days after discontinuation of treatment. Patient completely recovered with no remaining/residual symptoms or clinical findings of pharyngotonsillitis or symptomatic relapse at TOC.
Therapeutic failure	None or inadequate clinical effect during treatment period.
Not evaluable for primary outcome	Follow-up after discontinuation of treatment is missing.
Relapse	Symptomatic pharyngotonsillitis within one month after first diagnosis, according to clinical judgement by physician 1) antibiotic treatment necessary or 2) verified pharyngotonsillitis caused by streptococcus. Recurrent symptomatic pharyngotonsillitis presenting before and including the TOC visit, following at least 1 day without symptoms after initial treatment, will be judged as early relapse.
Complication with suspected relation to the primary infection	For example peritonsillitis, acute otitis media or sinusitis during the study period, i.e. until the last follow-up visit.
Bacteriological cure	Absence of GAS in culture. If culture is missing, a negative RADT.
Asymptomatic carriage of GAS	Presence of GAS in culture from patient *without* throat symptoms. If culture is missing, a positive RADT.
Symptomatic infection of GAS	Presence of GAS in culture from patient *with* throat symptoms. If culture is missing, a positive RADT.

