## Discussion

In the era of increasing antimicrobial resistance and the shortage of new antimicrobial agents it is necessary to revisit old antibiotics to ensure that they are used correctly and to their full potential. Important old drugs deserve to be rigorously tested according to today’s standards and requirements for clinical studies. Old antimicrobial drugs are often associated with inadequate knowledge on PK/PD and lack of optimized dosing regimens based on randomized controlled clinical trials.

Since old antibiotics are usually out of patent protection, financial incentives to perform the necessary studies are lacking. Thus, public funding is often the only option available [16]. For the current study, funded by the Swedish government, an initial systematic review to identify knowledge gaps was performed, followed by a structured prioritizing process by independent experts, in order to select the most needed non-clinical and clinical studies.

There is currently no substantial scientific evidence to recommend less than 10 days treatment of penicillin V against streptococcal pharyngotonsillitis. A shorter treatment period though, with lower total antibiotic exposure, is expected to reduce the risk of ecological disturbance on the human microbiota [17] and possibly improve patient adherence [13].

One possible disadvantage with a shorter treatment duration could be an increased risk for relapses, since the time with protection against a new infection is shorter. Furthermore, it could be argued that the daily dose for the 5-day treatment is slightly higher than the recommended daily dose, which may increase the risk for adverse events. However, there is extensive clinical experience of even higher doses in treatment of other infections like acute otitis media, sinusitis, and dental infection, justifying the safety profile of penicillin V also at high doses.

Overall we believe that this study, facilitated by public funding, may contribute with important knowledge and may have a substantial impact on public health. If a shorter and more potent treatment regimen is shown to be equivalent with the normal 10 day regimen this can imply great advantages for both patients (resistance, adverse events, adherence) and the community (resistance, drug costs).

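### Table 3 requires a symptom-free day only for relapses up to the test-of-cure visit, so persistent infection first re-treated or verified after that visit can be counted as relapse

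*Protocol article*

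**What the plan says.** All of this is in the protocol article.

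- **Definitions, Table 3, Relapse, first sentence.** Relapse is "Symptomatic pharyngotonsillitis within one month after first diagnosis, according to clinical judgement by physician 1) antibiotic treatment necessary" or "2) verified pharyngotonsillitis caused by streptococcus". The conditions are symptoms, a time window counted from diagnosis, and one of these two limbs. No earlier recovery is mentioned.
- **Same row, second sentence.** Recurrent disease "presenting before and including the TOC visit, following at least 1 day without symptoms after initial treatment, will be judged as early relapse". Here a symptom-free interval is required.
- **Table 3, Therapeutic failure.** "None or inadequate clinical effect during treatment period". The row stops at the end of treatment, and no row says whether failure excludes relapse or which takes precedence.
- **Primary outcomes.** "Clinical cure is defined as complete recovery without remaining/residual symptoms or clinical findings of pharyngotonsillitis or symptomatic relapse at TOC". Residual symptoms and relapse at TOC both count as non-cure.
- **Secondary outcomes.** The outcome is the "frequency of relapses one month after first diagnosis".
- **Discussion.** "One possible disadvantage with a shorter treatment duration could be an increased risk for relapses".

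**The concern.** The symptom-free condition in the second sentence shows that the authors meant to separate recurrence from persistence. They wrote it into only one half of the rule. After TOC the general sentence stands alone, and a patient who never recovered can satisfy every word of it.

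Relapse is the outcome that bears on the efficacy drawback the Discussion names for the short course. If persistent non-cures can enter it, a shortfall in cure at TOC is counted a second time and may be read as a separate tendency to relapse. Overlap between the two outcomes is not itself the problem: an early relapse is meant to be both a non-cure and a relapse. The problem is that patients in whom nothing recurred can be added to the relapse count.

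**Working it through.** **1. The rule applied to patient profiles.** All are symptomatic within one month of diagnosis.

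| Profile | First sentence | Second sentence | Result |
|---|---|---|---|
| Cured at TOC, later symptomatic with verified streptococci | met | not applicable (after TOC) | relapse, as intended |
| Symptom-free for a day or more, recurs by TOC, antibiotics judged necessary | met | met | early relapse, as intended |
| Symptoms unbroken, re-treated at or before TOC | met if read alone | governs this period; not met | not a relapse, if the specific sentence prevails |
| Symptoms unbroken, first judged to need antibiotics or first verified after TOC | met | not applicable (after TOC) | can be counted as relapse, though nothing recurred |
| Symptoms unbroken, neither limb met | not met | not met | not a relapse |

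The fourth row is the gap. The therapeutic failure row does not close it. A patient who improved adequately on treatment but still has symptoms at TOC is a non-cure without clearly being a failure, and even a clear failure is not barred from also being a relapse.

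**2. Where the gap lies in time.** TOC is 5–7 days after treatment ends, so about day 10–12 in the 5-day arm and day 15–17 in the 10-day arm. Taking a month as 30 days, the interval from TOC to the end of the relapse window is 30 − 12 to 30 − 10 = 18–20 days in the 5-day arm, and 30 − 17 to 30 − 15 = 13–15 days in the 10-day arm. The looser rule therefore operates about five days longer in the short-course arm. This locates the gap; it does not give its size.

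**3. The plan's own figure.** Inputs from Sample size/power calculation: 90% cure in both groups, margin 10 points, two-sided 95% confidence, 85% power, 1:1 allocation.

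n per arm = (1.960 + 1.036)² × (0.9 × 0.1 + 0.9 × 0.1) / 0.10² = 8.98 × 18 = 161.6, rounded up to 162. The total is 324, and 324 / 0.75 = 432. The stated figures reproduce, and this point does not touch them.

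**4. A ceiling on the misclassification.** Non-cures per arm = 162 × 0.10 = 16.2. Let f be the share of these with unbroken symptoms who first meet either limb after TOC. The document gives no value for f, so the full range is shown.

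| f (assumed) | Added per arm, 16.2 × f | Percentage points, 10 × f |
|---|---|---|
| 0% | 0 | 0 |
| 25% | 4.1 | 2.5 |
| 50% | 8.1 | 5.0 |
| 75% | 12.2 | 7.5 |
| 100% | 16.2 | 10.0 |

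The last row is a bound that should not be reached. The 16.2 includes true early relapses, patients re-treated by TOC, and patients with residual symptoms or findings who meet neither limb.

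**5. Effect on the comparison.** With the same f in both arms, the spurious relapse difference is f × (difference in non-cure). Under the plan's assumption of no difference it is zero in expectation. If, purely as an assumption, non-cure were 15% against 10%, it would be 5 × f: 1.25, 2.5 or 3.75 points at f = 25%, 50% or 75%, with no difference in true recurrence.

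**The case against.** The strongest reply is that the article already separates persistence from recurrence. Table 3 has its own failure row, the definition of cure names residual symptoms and relapse as different reasons for non-cure, the word relapse implies an earlier recovery, and a physician judges each case. A condensed article may also leave precedence between categories to the full protocol.

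Part of this stands. Several stronger readings that a reader might infer are not supported:

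- **That a second test is enough.** It is not. The second limb needs symptoms and verified streptococcal disease.
- **That re-treatment at the TOC visit exposes a contradiction.** The second sentence specifically covers events up to and including TOC and can fairly be read as governing them. Such a patient without a symptom-free day is then not a relapse.
- **That every never-cured patient who is re-treated is scored as a relapse.** The text allows it after TOC. It does not compel it, because a physician could treat the patient as a failure.
- **That relapse is overstated in both arms by a known amount.** The share is unknown and may be zero, and non-cures include true early relapses.

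The rest does not close the gap. The failure row ends with treatment. The judgement described in the first sentence concerns the need for antibiotics and does not ask whether the patient had recovered. The ordinary meaning of a word is a weak safeguard where a table sets out explicit conditions and applies the recovery condition to one period only. Nor is this merely an omitted detail: the article states the rule for a named secondary outcome, and the rule misclassifies when followed as written.

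**Conclusion.** The point holds for one group: patients with unbroken symptoms who first meet either limb of the relapse rule after TOC and within one month of diagnosis. They can enter the secondary relapse frequency although nothing recurred, so a difference in cure at TOC can reappear there.

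The size cannot be derived from the document. At 90% cure and 162 evaluable patients per arm it lies between 0 and at most about 16 patients per arm (0 to 10 points). The true figure is lower, because non-cure includes early relapses that are rightly counted. Any value inside the range rests on an assumed share.

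A reader might infer that the non-inferiority conclusion is at risk. It is not: persistence and relapse at TOC are both non-cure, so the primary outcome and the sample size are unaffected. The definition should be corrected because relapse is the outcome that speaks to the drawback the article itself names, and the correction is cheap.

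**What to change.** In Table 3, apply the symptom-free-day condition that now governs early relapse to every relapse, before or after TOC. Class symptomatic patients without such an interval as persistent infection or failure, and state that this category and relapse are mutually exclusive. Keep the full analysis set as the denominator for relapse, so that the comparison does not condition on cure.

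Clinical cure at TOC should not be made the entry condition for later relapses. It would exclude a patient with minor residual findings at TOC who then recovers fully and has a true recurrence. It would also exclude anyone without a TOC visit, where the plan allows for 25% not evaluable. And TOC falls about five days earlier after diagnosis in the 5-day arm, so the condition would apply at different points of the illness in the two arms.

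The cost is one clause in the definition and one extra category in the tables. There will be fewer relapse events. For events after TOC, the symptom-free interval has to be established from the diary (kept only until TOC), the TOC judgement and the 1-month call, so part of it rests on recall. Patients in whom the interval cannot be established should be counted and shown by arm.

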### Statistical analysis

#### Sample size/power calculation

The power calculation is based on the assumption of 90 % clinical recovery in the reference group and no difference between the two groups. The non-inferiority limit is set to minus 10%, the confidence level (two-sided) to 95 %, the power to 85 % and the distribution between the groups to 1/1. Based on these presumptions, 324 evaluable patients (162 in each group) are needed to be able to demonstrate non-inferiority between treatment groups. Presuming that 25 % of the included patients will not be possible to evaluate 432 (324*(1/0.75)) patients are needed to be included.

All effect variables will be analyzed for per protocol population (PP) as well as for the modified intention to treat (MITT) population as sensitivity analysis.

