## Abbreviations

CRF: Case record form
GAS: Gtreptococcus group A
GCP: Good clinical practice
ICH: International conference on harmonization
MIC: Minimum inhibitory concentration
MITT: Modified intention to treat population. Patients who received at least one dose of the study drug
PHC: Primary health care
PHCC: Primary health care centre
PK/PD: Pharmacokinetics and pharmacodynamics
PP: Per protocol population. Patients without violations to the study protocol, receiving at least 80 % of the prescribed study drug and evaluable at least until the TOC visit.
RADT: Rapid antigen detection test
RCT: Randomized controlled trial
TOC: Test of cure

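### Bacteriological eradication is not conditioned on GAS growing at baseline, so rapid-test-positive, culture-negative patients count as cures and any true difference between arms shrinks

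*Protocol article*

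**What the plan says.** All statements are in the protocol article.

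- **Outcome.** Secondary outcomes lists "bacteriological eradication according to the culture taken at the TOC". Only the TOC sample is mentioned.
- **Definition.** Under Definitions, Table 3 gives bacteriological cure as "Absence of GAS in culture. If culture is missing, a negative RADT". No baseline condition is attached.
- **Entry.** Inclusion criteria ask for 3–4 Centor criteria and "a positive rapid antigen detection test (RADT) for GAS will be included in the study". Culture plays no part in eligibility.
- **Baseline sample.** Visit one states: "A throat swab for semi quantitative cultures of streptococcus group A, C and G will be performed". Table 2 also schedules the culture at baseline and at TOC.
- **Analysis sets.** Under Sample size/power calculation: "All effect variables will be analyzed for per protocol population (PP) as well as for the modified intention to treat (MITT) population as sensitivity analysis". The abbreviations list defines MITT as "Patients who received at least one dose of the study drug" and PP as "Patients without violations to the study protocol, receiving at least 80 % of the prescribed study drug and evaluable at least until the TOC visit". Neither definition refers to the baseline culture.

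**The concern.** Eradication means that an organism present before treatment is gone afterwards. The stated rule looks only at the second half. A patient with a positive RADT whose baseline culture grew nothing, or only group C or G, and who has no GAS at TOC meets Table 3 and is counted as a success in PP and MITT.

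Randomization should spread such patients about evenly over the arms, so they raise both rates and pull any true difference towards zero. Eradication is the only microbiological outcome listed. If five days did clear GAS less often than ten, the reported comparison would understate the loss. The information needed to avoid this is already collected at visit one, but no stated outcome or population uses it.

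**Working it through.** **1. The plan's own figure.** The sample size rests on the "assumption of 90 % clinical recovery in the reference group and no difference between the two groups", a limit of minus 10 points, a two-sided 95% confidence level, 85% power and 1:1 allocation.

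n per arm = (1.960 + 1.036)² × 2 × 0.90 × 0.10 / 0.10² = 161.6, rounded up to 162. This gives 324 evaluable patients, and 324 / 0.75 = 432 to include. Both figures reproduce. They concern clinical recovery, so nothing below changes them.

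**2. Effect of the stated definition.** Let p be the true eradication rate among patients with GAS in the baseline culture, and f the share without it, the same in both arms and all negative at TOC.

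- Observed rate = p(1 − f) + f, an increase of f(1 − p).
- Observed difference = true difference × (1 − f).

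The shrinkage does not need every culture-negative patient to stay negative. If they are negative at TOC at any common rate in both arms, that term cancels and the factor is still (1 − f). The rates themselves are inflated as long as that common rate exceeds p.

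**3. Illustration.** The article gives neither f nor eradication rates. Assumed: 90% (10 days) and 80% (5 days), a true difference of 10 points.

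| Assumed f | 10 days | 5 days | Difference shown |
|---|---|---|---|
| 0% | 90.0% | 80.0% | 10.0 points |
| 5% | 90.5% | 81.0% | 9.5 points |
| 10% | 91.0% | 82.0% | 9.0 points |
| 15% | 91.5% | 83.0% | 8.5 points |

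For example, at f = 10%: 0.90 × 0.90 + 0.10 = 0.91, 0.80 × 0.90 + 0.10 = 0.82, and 0.91 − 0.82 = 0.09.

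**4. Effect on the confidence interval.** Assume 162 patients per arm have this outcome. The lower 95% limit for 5 days minus 10 days, with unpooled variance, is:

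- f = 0: −0.10 − 1.96 × √[(0.90 × 0.10 + 0.80 × 0.20)/162] = −17.7 points
- f = 5%, as written: −17.0 points
- f = 10%, as written: −0.09 − 1.96 × √[(0.91 × 0.09 + 0.82 × 0.18)/162] = −16.4 points

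With the denominator restricted to baseline culture-positive patients, the estimate is −10.0 points at every f. The lower limit is −17.9 points at f = 5% (162 × 0.95 = 153.9 per arm) and −18.1 points at f = 10% (162 × 0.90 = 145.8 per arm).

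**5. If some negative baseline cultures are false negatives.** Suppose half of the culture-negative patients did carry GAS and respond like the rest. Only the other half dilutes, so at f = 10% the factor is 1 − 0.05 and the difference shown is 9.5 points, not 9.0. The factor (1 − f) is therefore the full effect, reached when none of these patients had GAS.

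**The case against.** **It is a condensed article.** Table 3 gives one line per term, and the evaluable set for a secondary microbiological outcome could be settled in the full protocol or the SAP. This has some force. But the article does more than stay silent: it defines the outcome, sends all effect variables to PP and MITT, and defines both sets. A culture-positive denominator would add a condition that none of these statements contains.

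**Every patient has evidence of GAS.** Entry requires a positive RADT, and Table 3 itself accepts RADT where a culture is missing. Some culture-negative patients may have had GAS that the culture missed, and for them a negative TOC culture can be a real eradication. This stands. It makes the effect smaller, as in step 5 of the working, but does not remove it.

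**The size is hypothetical and small.** This also stands. Both f and the eradication rates are assumed, and 0.5 to 1.5 points would hardly change how a 10-point loss is read. If the arms truly do not differ, only the rates are inflated and the difference is unbiased.

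Two stronger readings are tempting, and the document supports neither:

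- *The definition inflates the risk of falsely declaring non-inferiority.* Applying the 10-point limit to eradication at a true 10-point deficit would raise that risk from 2.5% to 3.4% (f = 5%) or 4.5% (f = 10%). But the article sets the limit in the power calculation for clinical recovery and states no margin for eradication, so no formal decision is affected.
- *The same patients spoil the clinical-cure comparison.* The trial studies patients who qualify for treatment under current recommendations, that is, by Centor criteria and a positive RADT. Clinical cure in all of them is the question asked, so their inclusion is a choice of target population and not a flaw.

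**Conclusion.** The point holds for the secondary outcome of bacteriological eradication. As written, it measures absence of GAS at TOC among RADT-positive patients, not clearance of GAS found at baseline. Both rates are inflated and a true difference shrinks by up to the factor (1 − f): from 10 points to between 9.5 and 8.5 for an assumed f of 5% to 15%.

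This assumes that f is similar in the arms and that baseline culture-negative patients are negative at TOC equally often in both arms and more often than culture-positive ones. The actual f is unknown from the document and may be small. The primary outcome, the 324 and 432 patients, and the non-inferiority test on clinical cure are untouched. It is a modest but cheap correction.

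**What to change.** Define bacteriological eradication as GAS in the baseline culture and no GAS at TOC. Use patients with GAS in the baseline culture as the denominator, within both PP and MITT. State this in Table 3 and under Secondary outcomes, and carry it into the SAP. Report the present definition, including RADT in place of a missing culture, as a sensitivity analysis. Giving the number of baseline culture-negative patients per arm would let readers see f directly. An analysis of clinical cure in culture-positive patients is optional.

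The cost is wording and a slightly smaller denominator for this outcome: at an assumed f of 10%, about 146 instead of 162 per arm. The baseline culture is already taken, so no visit, sample or recruitment target changes.
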